Clinical research continues to demonstrate that patients in the placebo control arm of RCTs can have dramatic improvements. For example, recent meta-analyses on Parkinson’s disease (Goetz at al 2000), asthma (Joyce et al 2000), social phobia (Oosterbaan et al 2001), migraine (van de Kuy et al 2002), chronic fatigue syndrome (Cho et al 2005), symptom management (e.g., as pain and appetite) in oncology patients (Chvetzoff and Tannock 2003), sleep disorders (McCall et al 2003), restless leg syndrome (Fulda & Wetter 2007) and chronic pain (McQuay et al 1995) have all demonstrated that the response to placebo treatment in RCTs is dramatic and can be clinically significant. In fact, the high response to placebo treatment in RCT is the presumed reason why many widely used medications with well described physiological effects–- including antidepressants; analgesics, anxiolytics, antihypertensives, hypnotics, anti-anginal agents, angiotensin-converting enzyme inhibitors, -blockers, antihistamines, and nonsteroidal asthma drugs etc. are frequently indistinguishable from placebo in well-designed RCTS. (Temple & Ellenberg 2000, cf. Walach et al 2005)

3. Placebo Responses in IBS:

Similar to other illnesses, placebo responses in clinical trials involving patients with gastrointestinal disorders are high. (Musial et al 2007) Our team has published a meta-analysis (Patel et al 2005) that found that placebo responses in IBS clinical trials ranged between 16.0 to 71.4% with a population-weighted average of 40.2%, 95% CI (35.9, 44.4). More importantly, our team recently demonstrated in a RCT (n=262) that placebo treatment (sham acupuncture) combined with an augmented patient-practitioner context produced ‘adequate relief’ of IBS symptoms in 62% of patients compared to 28% in the wait-list control group (p<0.0001) (Kaptchuk et al 2008). The magnitude of this response is not only statistically significant but also clinically significant and comparable with current FDA approved medications for IBS.

4. Mechanistic Advances in Understanding Placebo Mechanism(s):

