#### F. DESCRIPTION OF RESEARCH PROTOCOL

#### Overview: This RCT seeks to determine whether non-deceptive (open-label) administration of placebo pill produces significantly more clinical improvement in IBS patients than an observation control.

#### Overall Design: Eighty patients with IBS will be randomized to a three-week course of either 1: non-deceptive open-label placebo pill in the context of positive expectation + usual care or 2. No treatment + usual care. Both groups will receive an equal amount of time with the practitioner. Patients will be assessed at baseline, mid-point and at the end of three weeks with the standard outcomes measures for IBS.

| Figure 1: Study Flow Chart  Open Label +usual care  (N=40)  No treatment waitlist+ usual care (N=40)  Baseline Evaluation and Randomization  (N=100)  Midpoint  Evaluation  Midpoint  Evaluation  3 Week Endpoint  Evaluation  3 Week Endpoint  Evaluation |
| --- |

Restatement of Research Question: A three-week course of non-deceptive open label placebo treatment will be produce statistically superior outcomes to a no treatment waitlist control group.

Design methodology and intervention:

Description of the non-deceptive placebo treatment arm: The intervention will

be geared to maximizing the contributions of positive expectation,

conditioning, adherence and a supportive and confident patient

practitioner relationship to the placebo response of IBS patients taking an

open-label placebo pill. The first phase of the discussion will be designed

to enhance expectation. Patients will be asked whether they have heard of

the placebo effect and what they think of it. After a brief exchange geared

to supporting any positive feelings the patient may have about placebo effects,

the practitioner will then talk about the evidence supporting the idea that just

taking placebo pills with a positive expectation initiates still poorly understood

effects that can have a profound impact of illness. It will be clearly explained that

placebo are made of "inert" substances like sugar pills but have been show

in clinical trials to improve patient symptoms. The practitioner will discuss

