**D. Data Analysis and Power Analysis:**

Outcome Measures: The following outcome measures will be used in this study. All questions will be asked at baseline, midpoint and endpoint with the exception of IBS-Global Improvement Scale (IBS-GIS) and IBS-Adequate Relief (IBS-AR).

IBS Global Improvement Scale (IBS-GIS): “Compared to the way you felt before you entered the study, have your IBS symptoms over the past 7 days been: 1) “Substantially Worse”, 2)”Moderately Worse, 3)”Slightly Worse”, 4)”No Change”, 5) ”Slightly Improved”, 6)”Moderately Improved” or 7) “Substantially Improved” (Kellow, 2003, Lembo, 2001; Gordon, 2003). A responder was defined as a patient who answered that their symptoms were either “moderately improved” or “substantially improved”. This will be our primary outcome.

IBS Global Symptom Assessment (IBS-GSA): Overall IBS symptoms will be rated by the subject by answering the following global question at the end of each week: Before you started taking the study “medication,” you said that you had [answer (in words) to baseline question 1 will be inserted here]. Compared to how you felt then, how would you rate your overall IBS symptoms during the past week? Possible answers are one of the following: Significantly relieved (+3);

Moderately relieved (+2); A little bit relieved (+1); Unchanged (0); A little bit worse (-1); Moderately worse (-2); Significantly worse (-3).

IBS Adequate Relief: Have you had adequate relief of your IBS symptoms over the past week? Yes or no

IBS Symptom Severity Scale (IBSSSS): The IBS Symptom Severity Scale (IBS-SSS) contains five questions that measure on a 100-point VAS, the severity of abdominal pain, the frequency of abdominal pain, the severity of abdominal distention, dissatisfaction with bowel habits, and interference with quality of life (Francis, 1997). All five components contribute to the score equally yielding a theoretical range of 0-500, with a higher score indicating worse condition. Previous studies have established that scores below 175 represent mild IBS symptoms, 175–300 represents moderate severity, and scores above 300 represent severe IBS (Francis, 1997). The total severity score on the IBS-SSS was treated as the gold standard measure of IBS severity. In the study by Francis et al., a decrease of 50 points correlatedwith improvement in clinical symptoms and was therefore considered to be a responder.

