**Mediation Analyses**

We also plan to conduct mediation analyses to determine whether any of the hypothesized mechanisms of the open-label placebo response (i.e., expectations, adherence, and the quality of the patient-practitioner relationship as measured by the WAI) can mediate the effects of experimental group assignment. For continuous variables (i.e., IBS-SSS and IBS-QoL), these analyses will take the form of analyses of covariance (ANCOVA), controlling for the influence of the mediators as well as the baseline symptom scores. For categorical outcome variables (i.e., IBS-AR, IBS-GSA, IBS-GIS) we will use logistic regression models. All analyses will be two tailed, with alpha set at .05. If the hypothesized mediators influence outcome, then the association between experimental group assignment (i.e., open-label placebo vs. wait list control) and outcome should significantly diminish or disappear altogether (in the case of complete mediation) once the mediators are added to the model.

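### Judging mediation of the categorical outcomes by shrinkage of a logistic group coefficient understates partial mediation, because odds ratios are non-collapsible

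*Protocol*

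**What the plan says.** The Mediation Analyses section of the protocol names three candidate mediators: "expectations, adherence, and the quality of the patient-practitioner relationship as measured by the WAI". IBS-SSS and IBS-QoL are to be analysed by ANCOVA with the mediators and baseline scores in the model. For the other outcomes the text is: "For categorical outcome variables (i.e., IBS-AR, IBS-GSA, IBS-GIS) we will use logistic regression models".

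One criterion then serves both model types. It opens "If the hypothesized mediators influence outcome, then the association between experimental group assignment" and concludes that the association with "outcome should significantly diminish or disappear altogether (in the case of complete mediation) once the mediators are added to the model". The testing rule is "All analyses will be two tailed, with alpha set at .05".

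IBS-GIS, one of the three categorical outcomes, is the primary outcome ("This will be our primary outcome", under Outcome Measures). Its between-group comparison is a separate chi-square test under Planned Statistical Analyses. The Mediation Analyses section gives no indirect-effect estimate and no effect scale other than that of the fitted model.

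**The concern.** In a linear model, adding a variable that group does not affect leaves the expected group coefficient unchanged, so a fall in the coefficient can be read as mediation. In a logistic model it cannot. Conditioning on any variable that predicts outcome moves the group log-odds ratio away from zero, even when group has no effect on that variable. The change in coefficient is thus the sum of a fall due to mediation and a rise due to rescaling.

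At stake is the mechanism claim for the responder outcomes. The same mechanism could appear to mediate IBS-SSS and IBS-QoL while seeming weaker, or absent, for IBS-GIS, only because one model rescales and the other does not.

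The criterion is also loosely worded. It makes shrinkage follow from the mediators influencing outcome, whereas mediation also requires that group changes the mediator.

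**Working it through.** The protocol gives no figure for the mediation analysis, so there is none to reproduce. The check compares a known mediated share with the shrinkage that the criterion would show.

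**Inputs**
- Responder rates: the team's earlier IBS trial reported adequate relief "of IBS symptoms in 62% of patients compared to 28% in the wait-list control group" (Placebo Responses in IBS). Used here as an illustration.
- Sample size: "Eighty patients with IBS will be randomized to a three-week course" (Overall Design), 40 per arm.
- Mediator strength: the protocol gives none. Assumed odds ratio per SD of 2, 3 or 4.

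**Model.** logit P(Y=1) = b0 + b·G + c·M, with M normal, SD 1, mean 0 in the control arm and mean a in the placebo arm. Y is a binary responder outcome, there is one mediator, and there is no unmeasured confounding. Averages over M are by Gauss-Hermite quadrature, and b0 and b are solved so that the marginal rates are 28% and 62%.

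**Unadjusted effect.** log-OR = ln(0.62/0.38) - ln(0.28/0.72) = 1.434 (OR 4.20). Risk difference = 0.62 - 0.28 = 0.34.

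**Definitions.** True share = 1 - (natural direct effect on the risk scale)/0.34. Apparent share = 1 - b/1.434.

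**Step 1: a variable unrelated to group (a = 0, true share 0).** The adjusted b is 1.584, 1.776 or 1.941 for OR per SD of 2, 3 or 4. Divided by 1.434, these are rises of about 10%, 24% and 35%.

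**Step 2: a real mediator.** Each cell gives the adjusted b and the apparent share.

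| True share | OR 2 per SD | OR 3 per SD | OR 4 per SD |
|---|---|---|---|
| 15% | 1.350; 5.9% | 1.513; -5.5% | 1.654; -15.3% |
| 25% | 1.197; 16.5% | 1.342; 6.4% | 1.467; -2.3% |
| 50% | 0.819; 43% | 0.917; 36% | 1.001; 30% |
| 75% | 0.429; 70% | 0.479; 67% | 0.522; 64% |
| 100% | 0; 100% | 0; 100% | 0; 100% |

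Example, OR 3 and a true 25%: 1 - 1.342/1.434 = 0.064. A negative share means that the coefficient grew.

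**Step 3: is this only a change of scale?** No. With a 25% share the natural direct effect is 0.75 × 0.34 = 0.255, so the placebo-arm rate with the mediator held at its control distribution is 0.28 + 0.255 = 0.535. On the marginal log-odds scale the share is 1 - [ln(0.535/0.465) - ln(0.28/0.72)]/1.434 = 1 - 1.085/1.434 = 24%, close to 25%. The gap down to 16.5%, 6.4% or -2.3% comes from conditioning on M.

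**Step 4: where shrinkage vanishes.** The coefficient does not move at all when the true share is 5.4%, 17.1%, 29.4% or 40.0% for c = 0.5, 1, 1.5 or 2. These are odds ratios per SD of exp(c) = 1.6, 2.7, 4.5 and 7.4.

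**Step 5: 40 per arm, 4000 simulated trials per row.** Proportion of trials in which the adjusted coefficient was not smaller than the unadjusted one:

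| c | a | True share | Logistic | Linear probability |
|---|---|---|---|---|
| 1 | 0.2 | 11.7% | 65% | 19% |
| 1 | 0.5 | 29.8% | 17% | 1% |
| 1.5 | 0.3 | 22.8% | 67% | 9% |
| 2 | 0.3 | 26.2% | 80% | 9% |
| 2 | 0.5 | 44.0% | 43% | 1% |

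The linear-probability column uses the same data on a collapsible scale, so sampling noise alone does not explain the logistic column.

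**The case against.** **The distortion is often modest.** A 75% share still shows as 64% to 70%, and complete mediation, which the protocol names, gives an adjusted coefficient of zero. This stands. A reader might infer that the rule generally hides or reverses mediation of the categorical outcomes. The table does not support that: within the assumed range, reversal needs a share of 25% or less and an odds ratio per SD of 3 or more.

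**The missing group-to-mediator path is not a second error of substance.** A reader might infer that variables unaffected by group would be declared mediators. Under a shrinkage criterion they would not be, systematically: the ANCOVA effect stays put in expectation and the logistic one grows. In linear models fitted to the same patients, the change in the group coefficient equals the product of coefficients, so the IBS-SSS and IBS-QoL point estimates are sound. What remains is the wording.

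**The text says association, not log-odds ratio.** A later SAP could standardise to risk differences without contradicting it. That is true, but comparing logistic coefficients is the natural reading, and a SAP that follows it inherits the bias.

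**A better method gains little power.** Requiring both paths to be significant, as a stand-in for an indirect-effect interval, simulation at 40 per arm gave power of about 50%, 41% and 31% for a 25% share (OR 2, 3, 4) and 18% for a 15% share at OR 3. This stands and belongs in the interpretation.

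**The analysis is secondary.** The aim and hypothesis concern efficacy only. A reader might infer that the primary result is at risk because IBS-GIS is involved, but its chi-square test does not use this rule.

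**The illustrative rates are borrowed.** They are adequate-relief rates from a sham-acupuncture trial, not IBS-GIS rates for an open-label pill.

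**Conclusion.** The point holds in a limited form. Read naturally, the criterion for IBS-AR, IBS-GSA and IBS-GIS is biased towards too little partial mediation. At mediator odds ratios of 2 to 4 per SD, the loss is about 7 to 20 percentage points for a true 50% share (50 - 43 and 50 - 30) and about 9 to 27 points for a true 25% share (25 - 16.5 and 25 + 2.3). An appearance of no mediation, or of the reverse, is confined to small shares with strongly prognostic mediators.

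The sizes rest on assumed rates of 28% and 62%, one normally distributed mediator, no group-by-mediator interaction and assumed mediator strengths. In every partial-mediation case computed under this model the direction is the same. The point is a method correction in a secondary mechanistic analysis and does not bear on the efficacy conclusion.

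**What to change.** - **Responder outcomes.** Replace the change-in-logistic-coefficient criterion with a standardised (counterfactual) indirect effect on the risk-difference scale. Fit a model for the effect of group on the mediator and an outcome model with group, mediator and baseline IBS-SSS, and report the indirect effect with a bootstrap 95% confidence interval.
- **IBS-SSS and IBS-QoL.** Keep the ANCOVA. Add a bootstrap 95% interval for the indirect effect, which supplies the missing test of whether the group effect significantly falls.
- **Wording.** State that mediation requires group to affect the mediator as well as the mediator to affect outcome.
- **Labelling.** Call the mediation results exploratory, and say that an interval including zero is not evidence against mediation.

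The cost is protocol or SAP wording and standard software, with no new data or visits. The downside is that intervals will be wide with 80 patients and small indirect effects will often be missed.

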the following characteristics: hand shaking, exchange on whether to use first or

last names, eye contact but not over gazing, courtesy, friendliness, orienting

the patient during examination, time for questioning, head nodding, forward

leaning, and uncrossed legs and arms. Empathy will be invoked with the

physician stating how he/she understands the difficulties that people with IBS

live with. Confidence will be fostered as the practitioner explains the

evidence concerning placebo effects. At the end of the first visit the patient will

be given enough placebo for the first half of the study and a mid-point follow-up

will be scheduled. The mid-point follow-up will be similar to the baseline

but abbreviated in time and will also include scheduling a final evaluation.

The entire discussion will take approximately 20 minutes.

Description of the no treatment usual care control arm:

The purpose of this arm is to match the ‘active” arm for time with practitioner. In

the informed consent, patients will be told that they will be randomized into

either the placebo or no treatment waitlist usual care arm. It will be explained,

if they are randomized to the latter, they will continue their regular IBS regimen

and will contribute to the observational IBS group. During the visits, t

he practitioners will seek clear descriptions of the patient’s symptoms

and life-style in relationship to their IBS. This evaluation will be in an identical context of the “active” arm with the exception that no attempt will be made to marshal positive expectation, conditioning response, or confidence of improvement or adherence to their IBS regimen. In order to fill the 20 minutes, the physician or nurse practitioner will provide educational support concerning IBS and go over the patient’s knowledge of IBS and how their life-style, including diet, exercise and stress contributes to their symptoms. We also review their current therapeutic regimen for IBS but we will not attempt to alter it during the study period.

Fidelity of treatment: To monitor fidelity to the time of treatments, the physician or nurse practitioner will put on a timer before the patient enters the room and turn off the timer after she/he leaves and record the time on the chart.

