Randomization- Group assignment will be determined based on results from program “Research Randomizer”. Randomization number will be given at time of visit. Allocation to group will be blinded until patient encounters the practitioner.

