**Other Measures:**

Expectations: Subjects will be asked to rate their expectations for improvement at baseline. Subjects will be asked: “At the conclusion of this three week trial how much to you expect your IBS symptoms to improve?” Their responses will be recorded on a 10 point scale with the following anchors: “0=No Improvement” and “10=Complete Relief of IBS Symptoms.”

Patient-Practitioner Relationship rating: The Working Alliance Inventory (WAI) scale will be used to measure the patient’s perception of the relationship with the practitioner. The WAI was developed by Horvath and Greenberg (1989) to measure three components of the patient-practitioner relationship: goal, task and bond. Data shows that WAI is reliably correlated with a variety of counselor and client self-reported measures.

Short Qualitative Description Report: At the completion of the study, after all assessment have been made patients who took the placebo will be asked to briefly describe in their own words responses to the following questions:

1. What do you think about the idea of taking placebo?

2. Did you expect it to work or were you skeptical?

3. What did you think was in the placebo pills?

4. Is there anything you would like to comment on about concerning your experience in the trial?

Subjects on the waitlist will be asked:

1. Were you disappointed to be in the waitlist?

2. What did the like the most and least about the trial?

3. is there anything else you would like to comment on about concerning your experience in the trial?

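### Pill adherence exists only in the placebo arm, so as a mediator of group it can make the group effect vanish through lost precision alone; the timing of the expectation rating is also left open

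*Protocol*

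**What the plan says.** The protocol's Mediation Analyses section names three mediators of group assignment: "expectations, adherence, and the quality of the patient-practitioner relationship as measured by the WAI". Continuous outcomes are analysed by ANCOVA, "controlling for the influence of the mediators as well as the baseline symptom scores". For the categorical outcomes, which include the primary IBS-GIS, "we will use logistic regression models". If the mediators influence outcome, the association between group and outcome "should significantly diminish or disappear altogether (in the case of complete mediation) once the mediators are added to the model". The section names no estimate or test of an indirect effect. The only criterion given is "All analyses will be two tailed, with alpha set at .05".

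Three other places bear on this:

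- **Adherence.** In the theoretical rationale and in the description of the placebo arm, adherence means taking the placebo pill as instructed. Controls receive no pill and keep their usual regimen. Their visits match the placebo arm's "with the exception that no attempt will be made to marshal positive expectation, conditioning response, or confidence of improvement or adherence to their IBS regimen".
- **Expectation.** Under Other Measures, "Subjects will be asked to rate their expectations for improvement at baseline". Under Randomization, "Allocation to group will be blinded until patient encounters the practitioner".
- **Relationship.** The Aim and the Overall Design match the arms on practitioner time. Neither says that WAI scores are matched.

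**The concern.** A variable can mediate the effect of group only if it is defined in both arms and can be changed by group. Adherence to a pill that one arm never receives fails the first condition. Entered beside group, it either removes the control arm or competes with group for the same information. The group term can then lose significance for reasons unrelated to mechanism, and the stated criterion invites reading that loss as mediation.

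An expectation rating made before the patient knows the allocation fails the second condition, because group cannot have changed it.

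This is the only quantitative test planned for the protocol's account of how open-label placebo works, in a trial meant to supply preliminary data for a larger grant. A misleading mechanism result would carry into that application.

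**Working it through.** **Inputs from the protocol.** 40 per arm (Overall Design); d = 0.5 to 0.9 and two-sided alpha 0.05 (Statistical Power). The mediation section gives no figure of its own to reproduce. As a check on the inputs, a two-sided t-test with 40 per arm and d = 0.5 has 59.8% power, against 60% stated. At d = 0.9 it has 97.8%, against 94% stated; that difference is a separate matter and does not enter here.

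**Assumptions not in the protocol.** Adherence coded 0 in controls; placebo-arm adherence with mean 0.8 to 0.9 and SD 0.1 to 0.2, capped to the range 0 to 1; no effect of adherence on outcome; correlation 0.5 between baseline and endpoint scores.

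**Case 1: adherence missing in controls.** Complete-case fitting leaves no controls. The design matrix (intercept, group, adherence) has rank 2 of 3, so the group effect cannot be estimated.

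**Case 2: adherence coded 0 in controls.** The adherence slope b is estimated in the placebo arm alone. The adjusted group effect is (arm difference) − b × m, where m is mean adherence. That is an extrapolation to a placebo patient who took no pills. With n per arm, residual variance σ² and adherence SD s:

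- variance before adjustment: 2σ²/n
- variance after adjustment: 2σ²/n + m²σ²/(n s²)
- ratio of standard errors: √(1 + m²/(2s²))

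Without the cap:

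- m = 0.90, s = 0.10: √(1 + 0.81/0.02) = √41.5 = 6.4
- m = 0.85, s = 0.15: √(1 + 0.7225/0.045) = √17.1 = 4.1
- m = 0.80, s = 0.20: √(1 + 0.64/0.08) = √9 = 3.0

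The cap shrinks the SDs to about 0.087, 0.130 and 0.173, which raises the ratios. Simulation of the planned ANCOVA with the cap, 4,000 trials per setting:

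| Adherence mean (SD) | SE ratio | Significance lost, d = 0.5 | Significance lost, d = 0.9 |
|---|---|---|---|
| 0.90 (0.10) | 7.6 | 93% | 91% |
| 0.85 (0.15) | 4.8 | 91% | 84% |
| 0.80 (0.20) | 3.4 to 3.5 | 86% | 74% |

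The last two columns are the share of trials with a significant group effect in which that effect is no longer significant once adherence is added. Repeat runs give about 74 to 94% overall; without the cap the range is 67 to 93%. The mean adjusted group effect stays close to d (0.48 to 0.50 and 0.89 to 0.91), so there is no bias, only lost precision.

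**Wider range.** With mean 0.85, SD 0.05 to 0.30 and d in residual-SD units, the SE ratio runs from 12.3 down to 2.7. Significance is lost in 83 to 94% of trials (d = 0.5) and 72 to 94% (d = 0.9).

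**The other mediators, same model.** An expectation rating unrelated to group (assumed coefficient 0.3) gives an SE ratio of 0.97, and power rises slightly, from 56% to 59% at d = 0.5. It creates no artefact, but it cannot carry the group effect either. A WAI that truly differs by 0.5 SD between arms (assumed coefficient 0.3) leaves the SE ratio near 1, and the group effect falls in part, as it should under real mediation.

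**Logistic models.** Responder rates of 28% and 62% (the waitlist and augmented-placebo rates quoted from the team's previous trial) give a log odds ratio of 0.490 − (−0.944) = 1.434. Conditioning on a covariate unrelated to group, with assumed log odds ratio 1.0 or 1.5 per SD, moves it to 1.724 (+20%) or 2.011 (+40%) with no mediation at all.

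**The case against.** The strongest reply is that the protocol states a conditional prediction, not a rule that loss of significance proves mediation: the group effect should shrink if the mediators influence outcome. In the simulation adherence has no influence, so the condition is false. If a significant adherence coefficient were also required, lost significance would coincide with one in only about 2% of the trials with a significant total effect. This stands in part. It rules out the stronger inference that false complete mediation would routinely be declared. It does not rescue the criterion, because the protocol names no test of the condition and none of the change in the group effect. Reading the size of the coefficient instead is no safer: among trials with a significant total effect, the adjusted group coefficient is at most half the unadjusted one in 33 to 43% (d = 0.5) and 24 to 39% (d = 0.9), with no mediation present.

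It can also be said that coding is undecided, that mediators might be entered one at a time, and that control adherence might mean adherence to the usual regimen. Separate entry does not help, since adherence alone produces the result. Adherence to another regimen is a different construct, and the protocol deliberately leaves it unpromoted in controls.

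A reader might go further and infer three things that the protocol does not support:

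- **That the WAI is matched by design and so cannot mediate.** Time is matched; expectation and confidence are not, and the supportive, confident relationship is part of the treatment in the Aim. WAI scores may differ by arm.
- **That expectation certainly cannot mediate.** The protocol also uses the word baseline for the visit that contains the script, so a rating after the script is compatible with the text. The fault is that the order is not stated.
- **That the logistic shift produces false mediation.** The shift is away from zero, so it can hide mediation rather than create it.

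**Conclusion.** The point holds for adherence. As a between-arm mediator it leaves the group effect either not estimable or, if controls are coded 0, estimated with a standard error about 3.5 to 7.6 times larger. A significant effect is then lost in about 74 to 94% of trials although adherence does nothing. These sizes rest on the assumed coding, mean and SD of adherence; the direction does not. The estimate stays unbiased, so the error lies in reading lost precision as mediation, which the stated criterion allows.

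For expectation the point is conditional: a rating made before allocation is revealed is a covariate or moderator, not a mediator. The WAI should stay as a candidate. Neither of these two produces false complete mediation.

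Severity is moderate. The analysis is secondary, and the primary IBS-GIS chi-square comparison is untouched.

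**What to change.** In the Mediation Analyses section:

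1. Remove adherence from the between-arm mediation. Report its association with outcome within the placebo arm, labelled as a non-randomised association.
2. Repeat the single expectation item after the first practitioner discussion and use that rating as the mediator, with the earlier rating as covariate. If it is not repeated, state that the baseline rating precedes the script and treat it as a moderator.
3. Keep the WAI as a candidate mediator.
4. Replace the criterion of a diminished or vanished group effect with estimated indirect effects and bootstrap 95% intervals. Use the risk-difference scale for binary outcomes, because logistic coefficients from models with different covariates are not comparable.

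The cost is one repeated question, reworded text and one mediator fewer in the between-arm model. With 80 patients the intervals for indirect effects will be wide, and the report should say so.
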